**Sex, n (%)**			
	Female	13 (68)	8 (44)
	Male	6 (32)	10 (56)
**Race, n (%)**			
	Non-White	1 (5)	0 (0)
	White	17 (89)	18 (100)
	Declined to answer	1 (5)	0 (0)
**Educational level, n (%)**			
	Some college or lower	3 (16)	2 (11)
	College degree	4 (21)	5 (28)
	Advanced degree	12 (63)	11 (61)
**Personal history of cancer, n (%)**			
	Metastatic breast cancer	5 (26)	4 (22)
	Advanced or metastatic ovarian cancer	3 (16)	1 (6)
	Metastatic prostate cancer	5 (26)	7 (39)
	Advanced or metastatic pancreatic cancer	6 (32)	6 (33)
**Previous testing, n (%)**			
	Yes	13 (68)	15 (83)
	No	3 (16)	3 (17)
	In process^c^	3 (16)	0 (0)

^a^In total, 11 participants reviewed visit 1 content, and 8 participants reviewed visit 2 content.

^b^Nine participants reviewed visit 1 content, and 9 participants reviewed visit 2 content.

^c^Had had pretest counseling or blood drawn but no disclosure.

We completed usability testing with 18 participants, 9 (50%) who completed the visit 1 intervention and 9 (50%) who completed the visit 2 intervention (Table 3). These participants used the digital intervention and were asked to comment on things that were confusing, functions that were challenging, and other changes they suggested. A research assistant viewed their navigation through cobrowsing software. Several function challenges were identified, prompting revisions to the intervention. These included addressing clearer instructions and labeling for arrows, hyperlinks, and hover functions and addressing how to return to the main content after accessing tier 2 content. Some minor changes to content addressed participant comments regarding typos, confusing terms, and increasing representation in images and content. Representative user comments that resulted in key changes to the intervention are described in Table 4.

**Table 4 table4:** Summary of key changes made during development and design of the web intervention based on user comments during user and usability testing.

Key changes recommended		Representative user comments
**User testing**		
	Simplify content	“Don’t like the small print. With ‘chemobrain’ this would be frustrating. Make it simple.”
	Address confusing content	“...where it says ‘unaffected family members have/will not have the option to pursue genetic testing.’ According to what? Needs more clarification.”
	Change order of the content	“Mention the glossary earlier on in the ‘how to use this website’ page so people know it is there from the get-go.”
	Move content to tier 2	“Would like it to be shorter—what do people really need? Maybe make tiered 1 info as short as possible (10 slides) and everything else tier 2.”
**Usability testing**		
	Clearer instructions and labeling	“Thought it would be nice to have text accompanying it [arrows] like the words ‘next’ and ‘previous.’”
	Hyperlinks and hover functions	“Would like cursor to change when hovered over the menu—to indicate that you could click on it.” “On iphone—can’t read instruction to hover over—too small.”
	Returning to main content from tier 2	Some confusion about tier 2 loops—sometimes the forward arrow gets you back to where you started. Sometimes there is only a back arrow.”
	Correction of typos and confusing terms	“‘Targeted therapy’ is not a phrase most people understand.” “Would expect more expanation or link to glossary for ‘microsatilite instability.’”
	Increase representativeness in photos	“Noted throughout the images were of older folks and predominately white. Felt it should be more diverse to normalize genetic testing for a wider audience.”

### Setting

Remote genetic counseling services in this study are provided through the Penn Telegenetics Program and Penn Cancer Risk Evaluation Program. The Penn Telegenetics Program has developed procedures for individual patients and health care providers across the nation to access remote genetic counseling services. For patients outside Pennsylvania, the Penn Telegenetics GCs collaborate with local health care providers to provide genetic services in the home. This model includes a physician registration process to facilitate this collaborative care model and has been successfully used in related nationally recruiting studies (NCT04455698 and NCT05427240). The Penn Telegenetics GCs are licensed in all US states as required by state licensure laws [40].

### Study Participants

#### Eligibility

Eligibility criteria include individuals diagnosed with metastatic breast or prostate cancer or advanced or metastatic ovarian or pancreatic cancer who are aged ≥18 years, able to understand and communicate in English, and residing in the United States. Exclusion criteria include uncorrected or uncompensated speech defects that would lead to the participant being unable to communicate effectively with a medical provider; uncontrolled psychiatric or mental conditions; or severe physical, neurological, or cognitive deficits rendering the individual unable to understand study goals or tasks. Participants who have already received cancer germline genetic testing are excluded.

#### Recruitment

Eligible patients can be referred by a health care provider or self-referred from a range of recruitment sources. First, at the University of Pennsylvania and affiliate oncology programs, members of the research team review treating physicians’ schedules to identify potentially eligible patients and, with health care provider permission, contact them for enrollment. Health care providers in these programs can also directly refer patients to the research team. Second, the Penn Telegenetics Program provides remote clinical services at several regional centers without GCs on-site. Clinical coordinators and health care providers at these sites identify eligible patients in their practices and refer them to the research team. Third, cancer-specific support groups (eg, Facing Our Risk of Cancer Empowered and Cancer Support Community) advertise the eREACH study through study flyers and website banners. Patients can contact the eREACH team and enter the study as self-referrals. Finally, in collaboration with the University of Pennsylvania Office of Clinical Research, the team posts Facebook advertisements on ClinicalTrials@Penn. Interested patients can enter the study as self-referrals.

Health care providers who refer eligible patients can complete an online permission-to-contact registration form to provide contact information for the patient. Research staff then contact the patient via phone or email, which includes the study purpose and procedures and a REDCap link to the electronic informed consent form and HIPAA document. Potential participants receive up to 5 contacts, typically 3 emails and 2 phone calls. Recruitment invitations began in September 2020.

#### Enrollment Goals

As outlined in the following sections, we initially planned enrollment of 560 participants (120 participants per arm). Given the low initial recruitment (2020-2023), which was attributed to the COVID-19 pandemic, and an increase in mainstream testing in oncology practices (oncology health care providers ordering genetic testing without GCs), we re-evaluated our initial enrollment goals (see the Data Analysis Plan section). In December 2023, we adjusted our enrollment goal to 60 participants per arm with baseline (T0) and postdisclosure visit 2 (T2) data (at least 240 in total).

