**Results:**

As of January 2025, we have completed enrollment of 229 participants. Data analysis is ongoing, and we expect the results to be published in 2025.

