We originally anticipated 140 participants per arm (560 in total). We chose our 2 primary variables as they demonstrated possible differences between groups in preliminary data from a prior study in which genetic test results were returned to patients; in this study, we expect that harmful changes will not occur. We will use a noninferiority test and, to be conservative, will require noninferiority in both the intention-to-treat and per-protocol analyses, as recommended [71].

With 140 people per arm, we have <1% noninferiority type I error and >82% noninferiority power if we simply use the first criteria that the *P* value must be >.15 and all 3 intervention arm coefficients must be >−0.25 (ie, in the direction away from being harmful when compared to the standard-of-care group). If we further apply the decision rule that the 85% one-sided CIs are bounded away from −0.35 if *P*≤.15, the power increases to 94%, and the type I error rate remains at <1%.

In calculating the type I error rate, we assumed that the 4–change score standardized means (standardized to have an SD of 1) for the null hypothesis were 0 (arm A=control group), 0.3 (single web intervention arms), and −0.6 (double web intervention arm), with negative values indicating a harmful effect. Our alternative hypothesis was a null effect (4–change score means of 0). These were conservative estimates of changes based on standardized RESPECT web intervention findings of a change score movement of 0.3 in anxiety and a change score movement of 0.4 in knowledge. Hence, we have excellent noninferiority power. Calculations were made using PASS (version 11; NCSS Statistical Software) in conjunction with R simulations (R Foundation for Statistical Computing). In secondary analyses, we will examine pairwise comparisons among the 4 arms using 2-tailed *t* tests.

In Multimedia Appendix 1, we provide the probability of declaring noninferiority under a range of assumptions about the intervention effects relative to the standard-of-care control arm. We see that our probability of declaring noninferiority is appropriate under several assumptions about population-level mean differences among arms.

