**Original assumptions (unconditional on observed data)**						
	No effect (power)	0	0	0	0	79
	Arm B and arm C beneficial	0	0.2	0.2	0	86
	Web intervention slightly beneficial	0	0.1	0.1	0.1	92
	Heterogeneous effects	0	−0.1	0.1	0	71
	Web intervention slightly harmful	0	−0.1	−0.1	−0.1	59
	Web intervention harmful—small effect	0	−0.2	−0.2	−0.2	36
	Web intervention harmful—relatively small effect	0	−0.25	−0.25	−0.25	25
	Web intervention harmful—modest effect	0	−0.3	−0.3	−0.3	16
	Only Arm B harmful	0	−0.35	0	0	23
	Web intervention harmful—moderate effect	0	−0.35	−0.35	−0.35	9
	Arm D very harmful (type I error)	0	−0.3	−0.3	−0.6	2

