## Results

IRB approval was obtained in June 2019 and recruitment began in August 2020. We have completed the enrollment of 256 study participants and data collection was completed in September 2024. Data analysis is ongoing and we expect results to be published in Fall 2025.

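### Table 5's 79% is the power for one endpoint in one analysis set with 60 complete cases per arm, not for the study; the joint power is not stated, and the success rule and enrolment figures need reconciling

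*Protocol article*

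**What the plan says.** **Target size.** Enrollment Goals sets the December 2023 target: "we adjusted our enrollment goal to 60 participants per arm with baseline (T0) and postdisclosure visit 2 (T2) data (at least 240 in total"). For the superseded target the same section says "we initially planned enrollment of 560 participants (120 participants per arm"), whereas Sample Size Justification for Aim 1 gives 140 per arm for the same total of 560.

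**Achieved size.** The abstract states: "As of January 2025, we have completed enrollment of 229 participants". The Results section states: "We have completed the enrollment of 256 study participants and data collection was completed in September 2024". Missing Data makes the primary analyses complete-case.

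**Power.** Table 5 (60 per arm, SD 1) presents its last column as the probability that the study as a whole is declared noninferior. The unconditional row "No effect (power") shows 79%. The blocks conditional on data to October 2023 show, under no effect, 99% for knowledge and 92% for anxiety.

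**What counts as success.** Primary Noninferiority Analysis names two primary outcomes, the T0-to-T2 changes in knowledge and anxiety, and takes an ITT approach with confirmation in secondary per-protocol analyses. Sample Size Justification for Aim 1 instead says the trial "will require noninferiority in both the intention-to-treat and per-protocol analyses, as recommended". Expected Findings hypothesises noninferiority for knowledge and anxiety together. The article does not say whether one endpoint is enough.

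**The concern.** A reader of Table 5 takes 79% as the chance that a harmless intervention leads to the trial's headline conclusion. If that conclusion needs both endpoints, and by one section both analysis sets, 79% describes only one component of it.

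The open rule matters in both directions. Requiring more components lowers power. Letting either endpoint suffice raises the chance of declaring noninferiority for a harmful intervention. Analysis was under way when the article was written, so the ambiguity bears on how the results will be read.

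The enrolment conflict adds to this. The target counts participants with T0 and T2 data, and one of the two reported totals is below that target before any attrition.

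**Working it through.** **Counts**
- Original target: 560 / 4 = 140 per arm; 4 × 120 = 480. So 120 is the slip.
- If 229 is right: 229 / 4 = 57.25 per arm, and 229 < 240, so the goal is missed even with no loss.
- If 256 is right: 256 / 4 = 64 per arm, and 240 / 256 = 93.75% must have both surveys.
- The 229 is not an interim count: it is dated January 2025, after data collection ended in September 2024. If 229 meant participants with both surveys, which the article does not say, the goal would still be missed by 11.

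**Decision rule simulated** (Primary Noninferiority Analysis). Let d_j = mean change in arm j minus mean change in arm A, for j = B, C, D, with pooled variance MSE.
- If the four-arm ANOVA F test gives P > .15: success when every d_j is −0.25 or better.
- If P ≤ .15: success when every one-sided 85% bound, d_j − t(0.85) × √(2·MSE/n), exceeds −0.35.

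Each figure uses 100,000 to 200,000 simulated trials.

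**Reproducing the plan.** One endpoint, one set, 60 per arm, SD 1, all means 0: 79.2-79.5%, against the stated 79%. All 11 unconditional rows of Table 5 reproduce within one point. At 140 per arm the rule gives 84% (first criterion) and 94% (full rule), against >82% and 94% stated. The published figures are therefore correct for a single endpoint in a single set.

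**Effect of the enrolment conflict alone** (one endpoint, one set): 78% at 57 per arm, 79% at 60, 81% at 64.

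**Both endpoints, ITT only, SD 1** (correlation between the two endpoints' change scores is an assumption)

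| Per arm | correlation 0 | 0.3 | 0.5 |
|---|---|---|---|
| 57 | 61% | 63% | 66% |
| 60 | 63% | 65% | 67% |
| 64 | 65% | 67% | 69% |

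Rough check at correlation 0: 0.79² = 0.62.

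**Both endpoints, ITT and per protocol, 60 per arm, SD 1** (per-protocol set nested in ITT, same true effect, loss in the digital arms only; the share is an assumption)

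| Per-protocol share | correlation 0 | 0.3 | 0.5 |
|---|---|---|---|
| 95% | 59% | 61% | 63% |
| 90% | 57% | 59% | 62% |
| 80% | 53% | 56% | 58% |

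This is the 53-64% range, to within simulation error. If the control arm lost the same share, it would be about 49-62%.

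**Higher T0-T2 correlation r.** With baseline SD 1, the change-score SD is √(2 − 2r): 0.894 at r = 0.6 and 0.775 at r = 0.7. At 60 per arm one endpoint then gives 84% or 89%. Both endpoints in ITT give 72% or 81% (endpoint correlation 0.3).

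**If either endpoint were enough.** With all digital arms at −0.25, Table 5 gives 25% for one endpoint (24.5% simulated). For either of two it becomes 43%, 41% or 38% at endpoint correlation 0, 0.3 or 0.5. Check at correlation 0: 1 − (1 − 0.245)² = 0.43.

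**The case against.** The strongest reply is that the 79% row is explicitly unconditional and is not the basis for stopping at 60 per arm. Sample Size Justification for Aim 1 rests that decision on the conditional results, 99% and 92% under no effect. These combine to little loss: whatever the dependence, the joint value lies between 0.99 + 0.92 − 1 = 0.91 and 0.92. This stands, and it means the unconditional ranges above are not the only relevant figures. It does not close the point. The conditional figures are also given per endpoint, assume 60 per arm, and come with no joint ITT and per-protocol result. They also lean heavily on data already seen: for knowledge, the figure stays at 93% even if future participants average −0.35 in every digital arm.

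Second, SD 1 may be pessimistic. The protocol says a T0-T2 correlation above 0.5 is likely, and joint power then improves materially. This also stands.

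Third, no sentence in the article makes success on both endpoints a decision rule, and an analysis plan not shown may set one. That is fair, but the two sections still contradict each other on per-protocol, and Table 5's label still claims more than the figure covers.

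A reader might infer that the real power is about 50-60%. The documents do not support that as a fact. It needs, all at once, a both-endpoint rule that is not stated, a per-protocol requirement that is disputed, an assumed per-protocol share, fairly low endpoint correlation and SD exactly 1. It also leaves out the conditional figures and the 64-per-arm case. Nor does the enrolment conflict drive the loss: it is worth one or two points.

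**Conclusion.** The point holds as a labelling and reconciliation defect with a material but assumption-dependent size. The 79% is correct for one endpoint, one analysis set, 60 complete cases per arm and SD 1; it is not the probability for the study.

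At 60 per arm under no effect and SD 1, the joint probability is about 63-67% for both endpoints in ITT (endpoint correlation 0 to 0.5). It is about 53-64% if both must also pass per protocol (share 80-95% in the digital arms). For both endpoints in ITT it is about 72-81% if the T0-T2 correlation is 0.6-0.7. If either endpoint sufficed, the chance of declaring noninferiority at −0.25 in all digital arms would rise from 25% to about 38-43%.

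Three contradictions need no assumption: 229 against 256 enrolled, 120 against 140 per arm, and per-protocol required against per-protocol secondary. The first leaves open whether the target was met, although its effect on power is small. The second concerns a superseded target and changes no analysis.

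**What to change.** - Reconcile 229 and 256, and report the number with both T0 and T2 data in each arm.
- Correct 120 to 140 per arm in Enrollment Goals.
- Make Primary Noninferiority Analysis and Sample Size Justification for Aim 1 agree that noninferiority must hold in both the ITT and per-protocol analyses, and state that both knowledge and anxiety must pass. Requiring both needs no multiplicity adjustment. Because data collection is complete and the statistician and principal investigator have seen unblinded data, cite the analysis plan if it already fixes this rule; otherwise date the clarification and say when it was made.
- Relabel Table 5's 79% as per endpoint and per analysis set. Beside it give the joint probability at the achieved number per arm, as a range over endpoint correlation, per-protocol share and T0-T2 correlation, together with joint conditional figures.

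Cost: text corrections, a rerun of the existing simulation and a less favourable stated power. No extra participants are needed.

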### Study Arms

#### Overview

Once participants have completed informed consent, the baseline (T0) survey, and family history collection with research staff, they are randomized into 1 of the 4 study arms. Randomization is stratified by sex and cancer type using a permuted block design within strata for randomization. The allocation sequence was generated by the study biostatistician and made available to research staff.

#### Pretest Counseling (Visit 1)

Participants in the genetic counseling arms (A and B) complete their pretest counseling session via phone or videoconference (according to patient preference) in their home or their selected location. Penn Telegenetics GCs use communication protocols adapted from related studies [18,43]. The Penn Telegenetics team contacts participants up to 5 times to schedule their pretest counseling session. If a scheduled participant does not show up for their appointment, they are contacted 3 times to reschedule. If visit 1 is not completed, the corresponding health care provider is notified (if the participant was health care provider referred). Participants who select videoconference are provided links to download secure videoconferencing software on their home computer or device. The Penn Telegenetics team uses a HIPAA-compliant technology platform for videoconference visits. In our communication protocols, if videoconference technology fails, GCs convert the session to phone.

Participants randomized to the digital intervention arms (C and D) are provided with instructions for obtaining a private code to access the pretest counseling digital intervention. Participants are informed that they can choose to schedule a counseling session with a GC if they do not wish to access the digital intervention or do not have online access. They can also ask to speak with a GC at any point.

Participants are asked to complete a post–visit 1 survey (T1) after completing counseling or the visit 1 digital intervention. While participants will be asked to complete the survey within 72 hours (3 days), surveys that are completed up to 7 days after consent are still accepted.

#### Genetic Testing

In all study arms, there are 3 available options for testing (Figure 4). Option 1 is a targeted panel limited to genes that could immediately impact treatment for metastatic cancer (*BRCA1* and *BRCA2* and Lynch syndrome). Additional homologous recombination repair genes will be tested for patients with prostate cancer based on the Food and Drug Administration label for the use of PARP inhibitors in this tumor type. Option 2 is a larger gene panel including additional genes related to their cancer type that could have an impact on treatment in the future or additional impact for relatives. Option 3 is a customized panel based on other health concerns or a desire to exclude particular genes. For option 3, participants are asked to speak with a GC to review their concerns and options. Those who log a decision on the digital intervention (arms C and D) have their selection, along with the details of their personal and family history, reviewed by their assigned study GC. In the event that the GC feels that an alternative decision for testing may be more appropriate (ie, the participant selects the targeted panel when a large or custom panel may be indicated), the GC calls the participant to confirm their decision. Self-referred participants are asked to provide contact information for an oncologist (or other health care provider) to serve as the ordering health care provider with the GC as required by state licensure laws. The Penn Telegenetics clinical team contacts the health care provider’s office to give them information about the program and procedures and confirm the health care provider’s information to include in the testing order.

Consistent with current clinical care, all genetic testing will be sent to a commercial laboratory (eg, Invitae or Ambry Genetics) and covered by insurance. At the time, laboratories would notify patients if out-of-pocket expenses of >US $100 were expected. Patients are instructed to contact the GC for any questions regarding coverage and cost. Test kits are sent to the participants’ home, and participants receive as many as 3 reminders to return their test kits. When requested, patients can have their samples collected at the University of Pennsylvania phlebotomy laboratory.

